## **c. Decentralized Medication Delivery**

Decentralized medication delivery through the “Centralized Chronic Medication Dispensing Distribution” (CCMDD) uses locations other than the clinic pharmacy to deliver medications to patients who are stable on treatment. Patients then only need to come to the clinic on a six monthly basis for a clinical exam. The goal is to reduce the burden on the patient in terms of the time and resources it takes them to collect their medication to improve treatment adherence and retention in care, while also decongesting the clinics.

| *Primary outcome:* | Proportion of patients eligible for decentralized medication delivery who receive all medications within the first 3 months after eligibility |
| --- | --- |
| *Eligibility:* | All adult patients who meet the criteria for being stable on ART (on same ART treatment regimen for at least 12 months; most recent viral load taken in past 6 months, 2 consecutive viral loads undetectable ) OR where a clinician confirms eligibility as a stable patient |
| *Sample size:* | 576 (288 per arm; 24 per cluster) |
| *Data sources:* | Tier.Net; pharmacy records; pickup point records or CCMDD registers or databases; other registers or records that document services provided during period of decentralized delivery |

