## **b. Adherence Clubs**

Adherence clubs comprise adherent and stable patients on ART who meet at facilities or identified locations in the community, in groups of up to 30 patients every two to three months to receive group counseling, have a clinical assessment, and receive the required supply of pre-packed medications. Adherence clubs are managed by lay staff at the health care facility with support from community health workers. The goal is to keep patients engaged in care and adherent to their medication by providing social support and facilitating medication delivery and treatment monitoring, while also reducing patient visit burden on the clinics[13]. The adherence guidelines SOP provides detailed instructions for establishing and running the clubs and for eligibility criteria and data collection.

| *Primary outcome:* | Proportion of patients eligible for participation in an adherence club who receive all medications within the first 4 months after eligibility |
| --- | --- |
| *Eligibility:* | All adult patients who meet the criteria for being stable on ART (on same ART treatment regimen for at least 12 months; most recent viral load taken in past 6 months, 2 consecutive viral loads undetectable ) OR where a clinician confirms eligibility as a stable patient |
| *Sample size:* | 576 (288 per arm; 24 per cluster) |
| *Data sources:* | Tier.Net; pharmacy records; club register; other registers or records that document services provided during the period of club observation |

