**Table 3. Evaluation outcomes**

| **Objective** | **Primary Outcome** | **Secondary outcomes** |
| --- | --- | --- |
| Fast track ART initiation counseling (Objective 1) | Proportion of patients who initiate ART within 30 days of becoming ART eligible (S) and the proportion of patients who are alive, in care, and virally suppressed (< 400 copies/ml^3^) within nine months of ART eligibility (L). | Proportion of patients who initiate ART within one week of becoming ART eligible  Demographic and clinical characteristics of patients who do and do not achieve primary outcomes (age, sex, baseline CD4 counts, TB diagnosis, other characteristics as allowed by data). |
| Adherence clubs (Objective 2) | Proportion of patients eligible for participation in an adherence club who receive all medications within the first four months after club eligibility (S) and the proportion virally suppressed (< 400 copies/ml^3^) at twelve months after club eligibility (L). | Proportion of patients consistently participating in club  Demographic and clinical characteristics of patients who do and do not achieve primary outcomes. |
| Decentralized medication delivery (Objective 3) | Proportion of patients eligible for decentralized medication delivery who receive all medications within the first three (S) months after delivery eligibility and viral suppression (< 400 copies/ml^3^) twelve months after delivery eligibility (L). | Proportion of patients consistently receiving medications  Demographic and clinical characteristics of patients who do and do not achieve primary outcomes. |
| Enhanced adherence counseling (Objective 4) | Proportion of patients with an elevated viral load who are alive, retained in care and resuppress their viral load (< 400copies/ml^3^) within three (S) and twelve months (L) of eligibility for enhanced adherence counseling. | Demographic and clinical characteristics of patients who do and do not achieve primary outcomes. |
| Early tracing of patients lost to follow up (Objective 5) | Proportion of patients eligible for early patient tracing who return to care within three (S) and twelve (L) months of eligibility. | Proportion of patients reached by tracers  Number of tracing attempts required; proportion of patients retained in care for at least one additional routine visit after tracing  Demographic and clinical characteristics of patients who do and do not achieve primary outcomes. |

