For all outcomes under Objectives 1-5 and 8, retention in care will be defined as (1-% attrition), with attrition calculated as the sum of reported deaths, loss to follow up, and reported transfers to other facilities. Retention will thus be interpreted as “retained in care at facility,” since the outcomes of patients who transfer will not be known. Where national identification numbers are available, the national death registry will be searched to locate unreported deaths. Loss to follow up will be defined as failure to attend the clinic within 90 days of a scheduled appointment, as stated in the Adherence Guidelines (Table 7 page 49).

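### Adherence clubs and decentralised delivery aim to keep patients in care, but their 12-month primary outcome is viral suppression alone, with no fixed denominator and no 12-month retention outcome for either cohort

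*Protocol*

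**What the plan says.** Section 4b says of adherence clubs: "The goal is to keep patients engaged in care and adherent to their medication by providing social support". Section 4c says decentralised delivery lightens the burden of collecting medication in order "to improve treatment adherence and retention in care, while also decongesting the clinics".

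Table 3 (section 10a) gives each objective a short-term (S) and a long-term (L) primary outcome:

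- Objective 2, long term: "and the proportion virally suppressed (< 400 copies/ml^3^) at twelve months after club eligibility (L".
- Objective 3, long term: "and viral suppression (< 400 copies/ml^3^) twelve months after delivery eligibility (L".
- Objective 1, long term: "the proportion of patients who are alive, in care, and virally suppressed", within nine months of ART eligibility.
- Objective 4, at three and twelve months: alive, retained in care and resuppressed.

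The secondary outcomes are consistent club participation for Objective 2, consistent receipt of medication for Objective 3, and for both a description of patients who do and do not reach the primary outcomes. Retention is not among them.

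Below Table 3 the protocol defines retention: "For all outcomes under Objectives 1-5 and 8, retention in care will be defined as" one minus attrition, where attrition is the sum of reported deaths, losses to follow-up and reported transfers. Section 10d analyses retention by arm overall, under Objective 6.

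**The concern.** Cohorts 2 and 3 are stable patients. They enter with two consecutive undetectable viral loads (section 8b) or, under sections 4b and 4c, on a clinician's confirmation of stability. Leaving care is therefore an important way for them to fail, and a patient who dies or leaves will usually have no 12-month viral load. The evaluation uses routine records only, so no study test can supply the missing result.

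If the 12-month proportion is taken among patients with a result, the comparison conditions on being in care and tested. That event occurs after randomisation, and both interventions are designed to change it. A benefit on retention would then be left out of the estimate. If the additional patients retained are less well suppressed than the rest, the benefit could even look like slight harm. No other outcome named for these cohorts would show the 12-month retention effect.

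**Working it through.** **Step 1: compare the outcomes.** Four objectives have a viral-load outcome. Two of them (1 and 4) require the patient to be alive and in care. The other two (2 and 3) do not, and no reason is given. The Objective 2 row names a population, patients eligible for a club, and attaches it to the short-term part. It then continues "receive all medications within the first four months after club eligibility (S) and the proportion virally suppressed", without restating the population or saying how patients with no result are counted. The Objective 3 row has the same structure.

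**Step 2: look for 12-month retention elsewhere.** The short-term outcomes stop at four months (Objective 2) and three months (Objective 3). Club participation cannot be compared with control clinics that do not implement the package. Consistent receipt of medication (Objective 3) has no time frame. The retention definition is written for Objectives 1-5, but no named Objective 2 or 3 outcome uses it. The Objective 6 analysis is pooled across cohorts, so it cannot isolate clubs or delivery.

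**Step 3: size of the difference between the two readings.** The protocol gives no 12-month retention or suppression rates, so all rates here are assumptions. Let r0 and r1 be retention in the comparison and intervention arms, s the suppression among patients who would be retained either way, and sx the suppression among the extra patients retained. Every retained patient is treated as tested.

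- Composite over all eligible: comparison r0·s; intervention r0·s + (r1 − r0)·sx.
- Tested only: comparison s; intervention [r0·s + (r1 − r0)·sx] / r1.

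With r0 = 0.85, r1 = 0.92 and s = 0.93, the comparison composite is 0.85 × 0.93 = 0.7905.

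- sx = 0.93: intervention composite 0.7905 + 0.07 × 0.93 = 0.8556, RR 0.8556/0.7905 = 1.08. Tested only 0.8556/0.92 = 0.930, RR 1.00.
- sx = 0.60: intervention composite 0.7905 + 0.07 × 0.60 = 0.8325, RR 1.05. Tested only 0.8325/0.92 = 0.905, RR 0.905/0.93 = 0.97.

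Other assumed rates give the same pattern:

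| r0 | r1 | s | sx | Composite | RR | Tested only | RR |
|---|---|---|---|---|---|---|---|
| 0.90 | 0.95 | 0.95 | 0.60 | 0.855 v 0.885 | 1.04 | 0.950 v 0.932 | 0.98 |
| 0.80 | 0.90 | 0.95 | 0.95 | 0.760 v 0.855 | 1.125 | 0.950 v 0.950 | 1.00 |
| 0.80 | 0.90 | 0.95 | 0.80 | 0.760 v 0.840 | 1.105 | 0.950 v 0.933 | 0.98 |
| 0.80 | 0.90 | 0.95 | 0.50 | 0.760 v 0.810 | 1.066 | 0.950 v 0.900 | 0.95 |

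The tested-only RR falls below 1 only when sx is below s. When the two are equal it is exactly 1, and the retention benefit is hidden rather than reversed.

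**Step 4: the other reading.** If the denominator is all eligible patients and a missing result counts as not suppressed, the present wording gives r0·s against r0·s + (r1 − r0)·sx. These are the composite figures, so nothing is lost.

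**The case against.** The strongest reply is that a tested-only denominator is nowhere stated. The Objective 2 and 3 rows open with eligible patients, and section 10c compares the proportion of subjects with the outcome between arms, which most naturally means all enrolled subjects. This stands. A reader might infer from Table 3 that a retention effect will be missed or will appear as harm. The text does not support that, because the effect depends on a denominator the protocol leaves open.

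A second reply is that denominators and missing-result rules are usually settled in an SAP, which is not shown here. That holds for the rule itself. It does not explain why the protocol fixes two different outcome definitions for comparable objectives, or why it names no 12-month retention outcome for two interventions meant to improve retention.

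Third, section 3c states Objectives 2 and 3 in terms of adherence and viral suppression, so the outcomes answer the questions posed. This is fair. Retention appears only in the stated goals of the interventions, so the choice of a composite is partly a choice of estimand.

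Fourth, early drop-out is caught by the short-term outcome, and the Objective 3 secondary outcome bears on continued engagement in both arms. Both points are correct, but neither gives retention at twelve months.

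Finally, the rates in the illustration are assumed, and apparent harm needs extra retained patients who are clearly less suppressed than the rest, although the cohort entered as stable. This also stands: the arithmetic shows what is possible and does not forecast a result.

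**Conclusion.** The point holds in a conditional form. What is certain from the text is that the 12-month primary outcome of Objectives 2 and 3 omits the alive-and-in-care condition used for Objectives 1 and 4, that neither cohort has its own 12-month retention outcome, and that the denominator for suppression is not fixed.

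Whether this distorts the result depends on that denominator. Under the main set of assumed rates, counting only tested patients gives RR 0.97 to 1.00 where the composite gives 1.05 to 1.08. Counting all eligible patients, with no result as failure, removes the problem. A primary outcome that allows two readings, which can differ in direction, should be settled before the data are analysed. It is a correction worth making and does not invalidate the design.

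**What to change.** In section 3c and Table 3, define the long-term primary outcome of Objectives 2 and 3 as alive, in care and virally suppressed at twelve months, with all eligible enrolled patients as the denominator, in line with Objectives 1 and 4. This also settles a small mismatch in timing: section 3c asks about suppression within twelve months, Table 3 at twelve months.

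For each of the two cohorts, report 12-month retention and suppression among those tested separately, so that the source of any difference can be seen.

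Two counting rules must be written down:

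- Reported transfers count as not retained, as the definition below Table 3 already implies, with a sensitivity analysis that excludes them.
- How patients who are retained but have no viral load are counted. The composite alone does not settle this, and Objectives 1 and 4 do not state it either.

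The cost is mainly wording. Visit dates and viral loads are on the list of data fields (section 9b), and deaths and transfers are already needed for the attrition definition. The sample sizes were set on the short-term outcomes (section 10b), so their stated basis does not change. The downsides are a lower headline success proportion and that transferred patients, some of whom may be suppressed, count as failures in the main analysis.

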## **d. Enhanced Adherence Counseling**

The goal of this intervention is to identify patients who have poor treatment adherence as indicated by an elevated viral load and target these patients for enhanced adherence counseling to help them improve their adherence. Although HIV-infected patients with detectable viral loads may receive additional adherence counseling under standard of care, this intervention will standardize and intensify that counseling. The intervention includes one or two structured education/counseling sessions in which effective strategies for achieving good adherence are discussed and goals set for viral re-suppression.

| *Primary outcome:* | Proportion of patients with an elevated viral load who are alive, in care and resuppress their viral load within 3 months of eligibility for enhanced adherence counseling |
| --- | --- |
| *Eligibility:* | All adult patients with a detectable viral load at a routine monitoring visit |
| *Sample size:* | 1008 (504 per arm; 42 per cluster) |
| *Data sources:* | NHLS laboratory database; Tier.Net; adherence plans; counselling registers or other registers or records that document provision of counselling |

## **e. Early Tracing of Patients Lost to Follow Up**

Early tracing of patients who miss an appointment by 5 days or more seeks to identify patients who have not returned to the clinic for scheduled appointments and attempts to return them to care. This intervention requires obtaining permission from patients to contact them and maintaining up to date contact information in patient records. The goal is to reduce clinic loss to follow up and improve patient outcomes by identifying those who have missed appointments and seeking to encourage them to return to care.

| *Primary outcome:* | Proportion of patients who miss a scheduled appointment by 5 days or more who return to care within 3 months of tracing |
| --- | --- |
| *Eligibility:* | All adult patients who fail to return for a scheduled appointment within 5 to 90 days from their appointment date |
| *Sample size:* | 576 (288 per arm; 24 per cluster) |
| *Data sources:* | Tier.Net; tracing registers or logbooks; appointment books; consent forms; other registers or records that document tracing attempts and interactions with patients |

In the early implementation phase at the study clinics, the government will also test fast track/spaced appointments for patients on antiretroviral therapy. This strategy is targeted at patients who are stable on treatment as defined above and therefore does overlap with the adherence club and decentralized medication delivery populations. If fast track/spaced appointments are implemented for the same patients enrolled in the adherence clubs or receiving decentralized medication delivery in the pilot facilities, the interventions evaluated will then be “adherence clubs plus fast tracked/spaced appointments” and “decentralized medication delivery plus fast tracked/spaced appointments,” as it will not be possible to distinguish between the impacts of the two interventions.

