- What is the effect of Enhanced Adherence Counselling on rates of being alive, in care, and virally suppressed within 3 and 12 months of intervention eligibility?

*Objective 5: Among HIV-infected patients in antiretroviral therapy programs who miss a scheduled appointment by 5 days,* ***evaluate the impact of Early Patient Tracing on retention in care****.*

Research questions:

- What is the effect of Early Patient Tracing on rates of returning to care by 3 and 12 months of tracing?
- What is the effect of Early Patient Tracing on rates of remaining in care by 12 months of tracing?

*Objective 6: For each clinic included in the study,* ***evaluate the overall impact of the Adherence Guidelines on patient outcomes****.*

Research questions:

- What is the effect of the package of interventions on patient retention in care overall?
- What is the proportion of population in need expected to benefit from the package of interventions?

*Objective 7:* ***Estimate the incremental and total cost of each of the interventions*** *listed above compared to standard of care.*

Research questions:

- What is the average cost per patient reached with the intervention?
- What is the average cost per successful outcome achieved?

*Objective 8:* ***Describe the current status of the cascade of care and adherence to treatment for tuberculosis, hypertension, and diabete****s, for the purpose of tailoring the minimum package of interventions to these conditions in the national rollout.*

Research questions:

- What is the prevalence of previously and newly diagnosed TB, hypertension, and diabetes among the population of patients presenting for care at primary health clinics, stratified by age, sex, and HIV status where possible?
- What proportion of diagnosed cases of these conditions are initiated on guideline-compliant treatment?
- What proportion of cases have satisfactory outcomes, based on current guidelines 12 months after diagnosis?
- For each condition, what proportion of patients are lost to care or discontinue treatment during the first 12 months after diagnosis?

Note that the impacts being assessed under Objectives 1-6 are the impacts of the interventions as implemented in the early phase of the national rollout of the guidelines. As is the case with program evaluations in general, results will reflect both intervention efficacy and implementation quality, which may in turn reflect the early learning stage of national policy implementation.

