Each of the interventions, while implemented as a package of services, will be delivered to a unique population within each clinic: patients newly eligible for ART, patients stable on ART, patients with poor adherence, and patients lost from care. (The exception to this is patients who are stable on ART and could be provided with either decentralized medication delivery or adherence clubs, but not both.) This will allow us to estimate the effect of each intervention individually, in the context of implementation of the overall minimum package. During the early stages of implementation of the Adherence Guidelines it is possible that eligible patients at intervention sites might not all be enrolled in an intervention they are eligible for. In order to ensure that this evaluation does not by chance exclude eligible patients who are exposed to the interventions, enrolment at intervention sites will include not only those eligible for the intervention but also eligible patients who receive the intervention.

The following five interventions will be evaluated under this protocol. Each is described in detail in the National Adherence Guidelines[11]. (Note: Additional details about primary and secondary outcomes, eligibility criteria, sample size, and data sources are included in later sections of this protocol.)

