- *Setting*. Both sites in each pair should draw from the same type of community: urban; informal settlement; or rural.
- *Location*. Pairs should be located relatively nearby one another, to facilitate data collection and increase similarity of the catchment populations.

- *HIV viral suppression*. The clinics in the pair should have ART patient viral suppression rates within 10% percent of one another (if data available).

Letters indicating Provincial and District Department of Health authorization to work at each study site have been obtained and are attached. The final number of clinics selected remains at 24 clusters.

In each pair, one clinic will randomly be assigned to receive early implementation of the minimum package of interventions, while the other will continue to provide standard of care. Randomization will be done through a random number generator in Microsoft Excel with a 1:1 ratio of allocation to intervention and control clusters.

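### Objective 5's primary outcome is timed from tracing in sections 3c and 4e but from eligibility in Table 3, and only the eligibility clock can be applied to every patient in both arms

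*Protocol*

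**What the plan says.** The protocol states the Objective 5 outcome in three places.

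- Section 4e, primary outcome row: "Proportion of patients who miss a scheduled appointment by 5 days or more who return to care within 3 months of tracing".
- Section 3c, research questions: "What is the effect of Early Patient Tracing on rates of returning to care by 3 and 12 months of tracing" and "What is the effect of Early Patient Tracing on rates of remaining in care by 12 months of tracing".
- Section 10a, Table 3: "Proportion of patients eligible for early patient tracing who return to care within three (S) and twelve (L) months of eligibility".

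The first two start the clock at tracing and the third at eligibility. Section 10c analyses each primary outcome already described and does not rank one definition above another.

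Four other statements bear on the point. In each matched pair one clinic gets the package "while the other will continue to provide standard of care" (section 8a). Section 4 expects that "eligible patients at intervention sites might not all be enrolled in an intervention they are eligible for". Cohort 5 is defined in section 4e as "All adult patients who fail to return for a scheduled appointment within 5 to 90 days from their appointment date". Section 9c starts enrolment in Cohorts 1-5 when eligibility is determined, and Table 2 requires the eligibility date for Objective 5.

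**The concern.** Early tracing is the intervention being randomised. A clock that starts at tracing has no start for three groups: comparison patients who are not traced under standard care, intervention-site patients whom the tracers never attempt, and patients in either arm who come back before anyone traces them. For those who are traced, the start date is itself a product of the assigned arm and of how quickly the clinic acts. An analyst who follows section 4e literally must improvise a rule for everyone else, and the rule chosen affects the result.

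This matters because section 10b sizes Cohort 5 on the short-term outcome. Table 3 also carries the short-term primary outcomes into Objective 6 and reports a cost per primary outcome achieved under Objective 7. If the clock is settled only at analysis, it could be chosen with the results in view.

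**Working it through.** **Step 1. Set the definitions side by side.**

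| Place | Who is counted | Clock starts | Horizon |
| --- | --- | --- | --- |
| Section 3c, return to care | Objective 5 cohort | Tracing | 3 and 12 months |
| Section 3c, remaining in care | Objective 5 cohort | Tracing | 12 months |
| Section 4e | Patients at least 5 days late | Tracing | 3 months |
| Table 3 | Patients eligible for tracing | Eligibility | 3 and 12 months |

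The denominators are all patients who missed the appointment or became eligible. None is limited to patients who were traced. In section 4 the other four interventions all have primary outcomes timed from eligibility, so 4e is the exception.

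**Step 2. Can each clock be applied in both arms?** Eligibility: yes. It follows from the appointment record, it starts enrolment (section 9c), and its date is a required field (Table 2). Tracing: no, for any patient without a tracing date. The protocol foresees such patients, since section 4 expects incomplete uptake and Table 3 lists the proportion reached by tracers as a secondary outcome.

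**Step 3. Illustrate the size.** No figure in the protocol is at issue, so there is none to reproduce. The following are assumptions, not protocol values: tracing has no effect; 30% return within 90 days of eligibility in both arms (Table 4 mentions 20-35% returning with little or no intervention); comparison patients are scored to 90 days after eligibility; intervention patients are scored to 90 days after a tracing date that falls d days after eligibility, with all returns up to then counted.

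*Pattern A, constant return rate.* h = -ln(0.7)/90 = 0.00396 per day. Share returned = 1 - exp(-h(90 + d)).

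- d = 14: 1 - exp(-0.00396 × 104) = 33.8%
- d = 30: 1 - exp(-0.00396 × 120) = 37.8%

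*Pattern B, quick and slow returners.* 15% of patients return quickly (mean 7 days). The other 85% return slowly, with 90-day probability 0.15/0.85 = 0.176, so hs = -ln(1 - 0.176)/90 = 0.00216 per day. Share returned = 0.15(1 - exp(-(90 + d)/7)) + 0.85(1 - exp(-hs(90 + d))).

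- d = 14: 0.150 + 0.85 × 0.201 = 32.1%
- d = 30: 0.150 + 0.85 × 0.228 = 34.4%

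Spurious difference from 30%, in percentage points, with a shorter and a longer delay added to show the range:

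| Delay to tracing (days) | Pattern A | Pattern B |
| --- | --- | --- |
| 7 | +1.9 | +1.0 |
| 14 | +3.8 | +2.1 |
| 30 | +7.8 | +4.4 |
| 60 | +14.8 | +8.5 |

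The design difference in Table 4 is 15 points.

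**The case against.** The strongest reply is that Table 3 is plainly the operative definition. Section 4 defers further outcome detail to later sections, section 10a introduces Table 3 as the list of outcomes to be measured, and enrolment and data capture are both built on eligibility. On that view 4e is loose summary wording and the biased scoring is not the planned analysis. Much of this stands: it shows which way to reconcile the text. It does not remove the conflict, because no sentence gives Table 3 precedence and 4e labels its own version the primary outcome.

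Three stronger readings are tempting, and the documents do not support them.

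- A reader might infer that the arms cannot be scored alike at all. That is true only of the tracing wording; Table 3's version can be scored the same way in both arms.
- A reader might infer that most comparison patients have no tracing date. The protocol does not describe what tracing standard care includes. The point needs only that some patients are untraced.
- A reader might infer that only traced patients will be analysed. No stated denominator says so. The effect of doing so also depends wholly on the assumed pattern: with tracing at day 14, pattern B gives 19.6% (10.4 points below 30%), while pattern A gives exactly 30%, no bias, because a constant rate has no memory. It should not be quoted as an expected bias.

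It is also fair that the delays and return patterns in the illustration have no source in the protocol, and that Table 4 words its 30% baseline as loss to follow up rather than return.

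**Conclusion.** Wrong as written. A sized primary outcome has two time origins in the current text. One of them is undefined for untraced patients and depends on the assigned intervention where it is defined. That conclusion rests on the wording alone.

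The size is illustrative. With no true effect and 30% returning within 90 days, a late clock in the intervention arm alone adds about 2 to 4 points at a 14-day delay and about 4 to 8 points at a 30-day delay, against a 15-point design difference. These figures hold only for the two assumed return patterns and for that particular mixed scoring. They are not a forecast of what the analysis will show, and an analysis that follows Table 3 would not incur this bias.

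**What to change.** 1. In the Objective 5 research questions (section 3c) and the primary outcome row of section 4e, count from eligibility instead of tracing, to match Table 3.
2. Define the eligibility date by one rule taken from the appointment record and applied identically in both arms. First reconcile the missed-appointment threshold: the Summary puts it at two weeks, sections 3c and 4e at 5 days, and sections 4e and 8b give a window of 5 to 90 days without saying which day in it counts. Which threshold applies is for the sponsor to settle.
3. State that every eligible patient is scored, whether or not traced.
4. Use tracing dates only for the secondary process outcomes, such as the proportion reached and the number of attempts.

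The cost is a wording amendment in a few places. The eligibility date and the scheduled and actual visits are already required fields, so no new data are needed. The change should be made before outcomes are analysed.
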